## Abstract

**Background:**

Snakebite envenoming (SBE) is an acute, life-threatening emergency in tropical and subtropical countries. It is an occupational hazard and a major socioeconomic determinant. Limited awareness, superstitions, lack of trained health providers, poor utilization of anti-venom results in high mortality and morbidity. India is the snakebite capital of the world. Yet, information on awareness, knowledge, and perceptions about snakebite is limited. Data on capacity building of health systems and its potential impact is lacking. Recommended by the National Task Force on snakebite research in India, this protocol describes the National Snakebite Project aiming for capacity building of health systems on prevention and management of snakebite envenomation in Maharashtra and Odisha states.

**Methods:**

A cross-sectional, multi-centric study will be carried out in Shahapur, Aheri blocks of Maharashtra, and Khordha, Kasipur blocks of Odisha. The study has five phases: Phase I involves the collection of retrospective baseline data of snakebites, facility surveys, and community focus group discussions (FGDs). Phase II involves developing and implementing educational intervention programs for the community. Phase III will assess the knowledge and practices of the healthcare providers on snakebite management followed by their training in Phase IV. Phase V will evaluate the impact of the interventions on the community and healthcare system through FGDs and comparison of prospective and baseline data.

**Discussion:**

The National Snakebite Project will use a multi-sectoral approach to reduce the burden of SBE. It intends to contribute to community empowerment and capacity building of the public healthcare system on the prevention and management of SBE. The results could be useful for upscaling to other Indian states, South Asia and other tropical countries. The findings of the study will provide critical regional inputs for the revision of the National Snakebite Treatment protocol.

**Trial registration:**

Registered under the Clinical Trials Registry India no. CTRI/2021/11/038137.

## Introduction

Snakebite envenoming (SBE) is one of the neglected tropical diseases (NTD) leading to around 81,410 to 137,880 deaths from 1.8 million to 2.7 million cases globally [1, 2]. SBE affects around 400,000 people every year causing permanent physical or psychological disabilities including blindness, amputation, and post-traumatic stress disorder [3]. It is estimated that in countries with a frail health system and scarcity of anti-venom, one death occurs every five minutes and four more people are disabled permanently due to SBE [4]. World Health Organization (WHO) classified SBE as a high-priority neglected tropical disease (NTD) in 2017, and subsequently, in May 2018, Seventy-first World Health Assembly (WHA) adopted a resolution providing a strong mandate to WHO for global actions on reducing the burden of SBE [5]. On May 23, 2019, WHA launched its roadmap to reduce the death and disability from snakebite by 50% by 2030 [4]. The strategy focuses on prevention of snakebite; provision of safe and effective treatment; strengthening health systems; and increased partnerships, coordination, and resources. Community education for seeking early and appropriate treatment, accelerating development and stockpiles of anti-venom, and stabilizing the market for snakebite treatments are also recognized as important aspects of this strategy [4, 6].

The recent national mortality survey [7] estimated that India had 1.2 million snakebite deaths (average 58,000/year) from 2000 to 2019 which is an increase of about 8000 cases/year compared to the earlier estimated survey (2001–2003). However, only a 10% coverage of the actual snakebite burden being captured in the government data in Maharashtra was also reported indicating gross underestimation of morbidity and mortality in Maharashtra [8]. The majority of the deaths occurred at home in the rural areas with half of the deaths happening between 30–69 years of age. Eight states (Madhya Pradesh, Odisha, Uttar Pradesh, Bihar, Jharkhand, Rajasthan, Gujarat, and Andhra Pradesh including Telangana) of India shared the burden of about 70% snakebite deaths from 2001 to 2014 [8]. A nationally representative mortality survey conducted by Mohapatra B et al 2011, included Maharashtra in the high prevalence of snakebite envenomation (SBE) group with an age standardized mortality rate of 3.0 per 100000 people. Except the high prevalence states, for the rest of the country the age standardized mortality rate was 1.8 per 100000 people during the same period. In the same study, Maharashtra was also reported to have the fifth largest number of deaths due to snakebite among the high prevalence states [9]. Snakebites usually occur in geographically remote areas and hence their burden either goes unnoticed or is underreported [10]. From 2003 to 2015, the million death study estimated about 154,000 snakebite deaths in both private and public hospitals. However, the government reported only 15,500 hospitals deaths indicating that only about 10% of the expected deaths were captured [7].

SBE is labelled as a disease of poverty [11]. Agricultural and migrant workers, tribes, hunters and often, the earning members of the family are the victims. So it is not only a public health problem but also a major socio-economic determinant in India [12]. A study conducted in the tribal region of Maharashtra, India, reported 4.5% case fatality rate [13] while a study in rural Nepal reported an annual incidence of 1162/100000 with an annual mortality rate of 162/100000 due to SBE [14]. A meta-analysis of data from 41 Sub-Saharan African countries estimated the annual burden of SBE related deaths as 1.03 million DALYs, higher than the burden of many NTDs globally [15]. Similarly, a study in West Africa revealed a higher burden of SBE compared to other NTDs found in 16 countries and labelled SBE as underappreciated [16].

SBE burden coupled with a lack of awareness amongst the Medical Officers (MOs) and other healthcare providers about the National Snakebite Management Protocol (2009) and Standard Treatment Guidelines (STG, 2017) creates major hurdles in management of SBE [13]. An irrational usage of anti-venom skin test was also reported in the tribal block of Dahanu, Maharashtra [17]. Primary Health Centers in rural India face a multitude of problems including the acute shortage of trained human resources, unavailability of anti-venom and emergency ventilation services [18]. Issues with public health facilities and geographical inaccessibility supplemented by superstitions and cultural beliefs regarding snakes force SBE victims to seek care from faith healers [19, 20]. Studies in rural and tribal areas have revealed inadequate knowledge about venomous snake identification and faith healers were the first choice for about 38–68% of people for SBE management [17, 21–24]. Most of the traditional and herbal methods of first aid and management of snakebite have been found to cause more harm than benefit [25, 26]. Proper knowledge of snakes and snake-bite management was also found to be either diminutive or absent in the majority of participants as reported by a study from Haryana [27]. Fear, negativity, and unfamiliarity regarding prevention and ambivalent opinions on health-seeking are known drivers of people’s perception of snakes and snakebites [28]. These findings strongly suggest the need for community awareness on the prevention and first aid of snakebite and empowerment of frontline healthcare workers and Medical Officers for effective management of SBE in public healthcare settings.

Previously, the authors have established a successful model for the prevention and management of SBE at Dahanu block of Palghar district through the Model Rural Health Research Unit (MRHRU) [13, 21]. The model involved community awareness, training of healthcare workers, snake handlers, and faith healers, availability of anti-venom and, implementation of the National Snakebite Treatment Protocol. Indian Council of Medical Research (ICMR)-National Task Force Expert Group for ‘Research on Snakebite in India’ recommended upscale of the Dahanu model to a Health System Research project using a similar multi-sectoral approach for attaining the 2030 goal set by WHO. Based on those recommendations, this protocol was developed and it describes the National Snakebite Project that aims for prevention and management of SBE in selected districts of Maharashtra and Odisha.

The objectives of the study are:

To increase the awareness and empower the community on prevention, first aid, and early transport of snakebite patients to the nearest health facilityTo evaluate the healthcare providers regarding their knowledge and practices during management of SBE and understand the anti-venom distribution and utilization at public health facilitiesTo empower the health system for management of SBE through the implementation of Standard Treatment Guidelines (STG) of the Government of IndiaTo study the impact of the interventions on reducing the SBE mortality and morbidity

## Materials and methods

### Study scheme

The interventional study has retrospective, prospective, cross-sectional, and qualitative components and will be conducted in a community as well as hospital settings (Fig 1). It is divided into five phases (Fig 2). Phase I involves collecting retrospective data of snakebites, facility surveys, and focus group discussions (FGDs) in the community. Phase II is to increase awareness and empower the community on prevention, first aid, and early transport of snakebite patients to the nearest health facility. Phase III will be to evaluate the basic knowledge on snakebite management and anti-venom utilization among healthcare providers. Phase IV is to empower the health system for management of SBE and optimal utilization of anti-venoms through training programs and Phase V will focus on the impact evaluation of the health system and community interventions using FGDs and comparison of pre-and post-intervention data.

**Fig 1 pone.0281809.g001:**
[figure not shown]
Timeline of the study.

**Fig 2 pone.0281809.g002:**
[figure not shown]
The outline of the study.

### Study setting

From 2001 to 2014, Odisha and Maharashtra bore the burden of about 40300 and 56000 snakebite deaths with an age-standardized death rate of 6.7 and 3.5 / 100000 respectively [8]. Deaths between the age of 5 to 14 years were greater in Odisha while deaths among females were prominent in Maharashtra [8]. SBE has been a chronic problem in these two states with an earlier county-wide survey (1941–1945) suggesting that compared to other states, snakebite mortality is a greater problem here as the majority of geographical areas are forested and infested with snakes [29]. The proposed study is a multi-center study that will be conducted in the West and East Zones of India. Under the West zone (Maharashtra state), two blocks namely, Shahapur in district Thane and Aheri in district Gadchiroli will be included. Under the East zone (Odisha state), two blocks namely, Khordha in district Khordha and Kasipur in district Rayagada will be included (Fig 3, Table 1). The population in the study areas lives with an absolute risk of ≥0.5% of dying due to snakebite before the age of 70 years with the risk being highest in Aheri and Kasipur [8].

**Fig 3 pone.0281809.g003:**
[figure not shown]
Geographical location of study areas of Maharashtra and Odisha states in India. Source: AMCHARTS SVG Maps; https://www.amcharts.com/svg-maps/?map=india2019. Permission obtained for use.

**Table 1 pone.0281809.t001:** Demographic details of the study areas in Maharashtra and Odisha.

Parameter	Shahapur block	Aheri block	Khordha block	Kasipur block
Coordinates	19.45°N 73.33°E	19.41°N 80.00°E	20.16°N 85.66°E	19.22°N 83.08°E
Population	314103	116992	139978	70542
Living in rural areas	77.5%	87.5%	67%	100%
Scheduled Tribes population	35.7%	49.8%	8.4%	58.8%
Female literacy	58.41%	55.67%	73.22%	20.35%
Sex ratio	957	986	935	1071
Workers engaged in marginal activities*	27.6%	29.8%	25.5%	60%

All data sourced from—Census of India 2011. Registrar General and Census Commissioner of India. https://www.censusindia.co.in/. Accessed 24 April 2022.

*Marginal activities provide livelihood for less than six months in a year. Proportions out of total working population in the block

### Framework for the study

#### Roles and responsibilities

The study coordinator will ensure the smooth and ethical conduct of the study. The site Principal Investigators and the project staff will be responsible for study site conduct. A Technical Advisory Committee (TAC) will be constituted steering the study. The TAC will comprise of national and regional experts in the area of snakebite management who have contributed to the development of STG, 2017. National and State Program Managers, Public Health Department members, social scientists, public health experts, herpetologists, forest departments will also be included in the study.

#### Development of data collection tools and their validation

The data collection tools will be developed by public health experts based on a review of available literature, standard treatment guidelines for snakebite, and consultation with the TAC.

*Retrospective and Prospective data form*. These two data collection forms will include questions about the basic demographic characteristics of the snakebite victim followed by details of the event of snakebite, signs and symptoms, first aid, and steps taken for the management including usage of anti-venom. The forms will have a separate ‘Follow Up’ section for transferred out patients. Hospital records will be used for form filling.

*Facility Survey Questionnaires*. Separate questionnaires will be developed for Primary Health Centre (PHC), Rural Hospital (RH) / Community Health Centers (CHC), and Sub District Hospital (SDH) / District Hospital (DH) to document staff positions, drugs, equipment, anti-venom availability and utilization, infrastructure, laboratory investigations, and Information Education Communication (IEC) materials and activities. The questionnaires will concur with the Indian Public Health Standards (IPHS) Guidelines and STG, 2017 for respective facilities.

*Focused Group Discussion (FGD) Guide*. The FGD guide will consist of open-ended, semi-structured questions to elicit the knowledge, awareness, and perceptions of people in the study area regarding snakes and snakebites, first aid, prevention methods, management, and health-seeking behavior. The FGD guide will be developed in English and later translated to local languages.

*Questionnaire for healthcare providers*. Separate questionnaires for peripheral workers and Medical Officers (MO) at facilities would be developed based on the STG, 2017 and WHO SEARO Guidelines for management of snakebites. They will try to capture the knowledge, perceptions, and experiences of healthcare providers regarding snakes and snake bites, anti-venom use, challenges encountered while managing snakebite cases at public health facilities.

All the developed tools will be validated through the following methods–

*Face Validity*. The TAC will critically review the tools to confirm that they have sufficient and pertinent information to gather the knowledge, awareness, and perceptions of the respondents. The panel will be asked to comment on the relevance, language, ease of understanding, and ability of the questions to elicit desired responses.

*Content validity*. Each item on the questionnaire will be rated based on a four-point Likert scale ranging from ‘Not Relevant to ‘Highly Relevant. Based on the rating given by experts, Item Level Content Validity Index (I-CVI) will be calculated. Items with an I-CVI value of 0.8 or more will be included in the final version [30].

*Construct validity*. A pilot study of the tools in a demographically similar population will be carried out to examine the degree to which the observations concur with the investigator’s hypothesis and will make way for further revisions of the tools.

*Readability*. To confirm the understanding of the questions, the Simple Measure of Gobbledygook (SMOG) score will be used.

*Difficulty index*. Any question that is unclear to the participants will be identified and reworded by taking the percentage of correct responses overall. Questions unclear to 50% of participants will be rewritten.

In addition, all the research tools will be pre-tested in a similar population and revisions would be made based on the pre-test findings before actual use in the study.

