### Statistical analysis

The baseline data will be analyzed separately for different strata (Gender-wise, Age-wise, seasonal variation, distribution of venomous and non-venomous snakebite, site of snakebites, and categorization of snakebite based on the sign and symptoms of envenomation). The differences across strata will be investigated using appropriate statistical tests based on the nature of the variables. The Chi square and Fisher’s Test would be used to compare categorical variables while the independent t-test would be used to compare continuous variables. To check the factors associated with the incidence of snakebite, bivariate regression models will be used and results will be presented through odds ratios. The primary outcome will be reduction in the incidence of snakebite cases per 100000 population and a reduction in the case fatality rate in the study areas at the end of two years, measured by comparing the pre- and post-intervention data on the incidence of snakebite and mortality in the four study blocks. The secondary outcomes will include reduction in mean bite to needle time, reduction in the proportion of snakebite victims referred to higher facilities for management, increase in the proportion of MOs providing treatment as per STG 2017, mean increase in the number of vials of anti-venom administered to victims, reduction in the proportion of cases with severe complications including reduced kidney failure and amputation rate. Data from interviews of healthcare providers will be analyzed further for frequency. A summative index will be developed from the knowledge test of health workers. Two sample t-test will be used to compare the change in the knowledge of Medical Officers and the healthcare workers after the training. A p-value < 0.05 will be considered statistically significant. All the quantitative data will be entered and analyzed using the statistical package SPSS (version 26.0; IBM Corporation, Armonk, NY, USA).

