## Discussion

SBE remains a major public health hazard predominantly in tropical countries [3]. In Asia up to two million people are bitten by snakes every year; the majority of them are women, children, and poor rural communities [32]. SBE has highly effective treatment and severe complications can be prevented with a correct dose of anti-venom [33]. Snakebite treatment remains a complex issue in countries like India due to various factors—poor community knowledge, ill-equipped hospitals, treatment accessibility, travel time, and reliance on faith healers for treatment [34]. Very little attention is drawn towards the assessment of basic knowledge of medical doctors on management of snakebite and its complications [35, 36].

A study conducted in India and Pakistan concluded that standard protocols and training are required to empower doctors to reduce snakebite mortality [35]. Another study from Bangladesh revealed that peripheral healthcare workers lack knowledge, experience, and adequate skills required to treat snakebite victims [37]. In a recent study from Bhutan, only 25% of health workers had adequate knowledge of snakebite management. However, 63% of medical doctors were found to have adequate knowledge compared to other healthcare workers [23]. A study in Haryana on farmers, teachers, medical residents, and students reported that only 13% participants, were aware of the ‘big four’ snakes [27]. Lack of appropriate knowledge on snakes, first aid, treatment, and prevention among the clinicians was also reported in northern Nigeria [38]. In Hong Kong, only 29% of clinicians were confident about treating snake bites [36].

India is a major manufacturer of anti-venoms. However, there is a paucity of satisfactory data regarding the number of anti-venom vials needed to reverse the clinical effects of SBE [39]. Passivity, inaction and supply-demand incoordination have resulted in both unavailability and inadequacy of anti-venom marginalizing the effective cure to SBE [40]. A study in Africa reported that compared to requirements, the number of effective treatments available for SBE might be as little as 2.5% [41]. In many African and Asian countries, anti-venom production is either at standstill or stopped altogether [42].

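### The difficulty-index rule judges whether a question is clear by the percentage of correct answers, which cannot separate poor wording from lack of knowledge

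*Protocol article*

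**What the plan says.** The protocol article, under Development of data collection tools and their validation, lists several checks and applies them to every instrument: "All the developed tools will be validated through the following methods". One check is the difficulty index: "Any question that is unclear to the participants will be identified and reworded by taking the percentage of correct responses overall". The next sentence gives the trigger: "Questions unclear to 50% of participants will be rewritten". Percentage correct is the only measure named for this rule.

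One of the instruments covered is the questionnaire for healthcare providers, with separate forms for peripheral workers and Medical Officers. Of these forms the section says: "They will try to capture the knowledge, perceptions, and experiences of healthcare providers regarding snakes and snake bites". On piloting it says: "A pilot study of the tools in a demographically similar population will be carried out".

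The items have two later uses. Gaps found in Phase III feed into the Phase IV training. The Statistical analysis section adds: "A summative index will be developed from the knowledge test of health workers", and the change in knowledge after training is then tested.

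**The concern.** A wrong answer to a knowledge question has at least two causes: the respondent did not understand the question, or understood it and did not know the answer. Percentage correct mixes the two. A rule that takes it as the sign of an unclear question will pick up well-worded items on material that people have not learned, and that is what Phase III sets out to measure. A pilot group similar to the target population can be expected to have the same gaps.

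At stake are the Phase III description of provider knowledge and the before-and-after comparison on the summative index. If an item is rewritten because most people got it wrong, and the new wording is easier or hints at the answer, the baseline score rises, the gap looks smaller and less room is left for improvement.

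**Working it through.** The plan derives no figure here, so there is nothing to reproduce. Three checks show how the rule behaves.

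**1. A clear item that few can answer.** Read the rule as flagging an item when at least half of the pilot answers are wrong. Let p be the share who know the answer and suppose nobody misunderstands the question. The chance of flagging is P(X ≥ n/2), with X ~ Binomial(n, 1 − p). The pilot size is not stated in the article, so n is assumed.

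| p (share correct) | n = 20 | n = 30 | n = 50 | n = 100 |
|---|---|---|---|---|
| 0.13 | 1.000 | 1.000 | 1.000 | 1.000 |
| 0.25 | 0.996 | 0.999 | 1.000 | 1.000 |
| 0.40 | 0.873 | 0.903 | 0.943 | 0.983 |
| 0.50 | 0.588 | 0.572 | 0.556 | 0.540 |
| 0.63 | 0.165 | 0.101 | 0.041 | 0.005 |
| 0.80 | 0.003 | 0.000 | 0.000 | 0.000 |

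Three of these values of p are borrowed from the Discussion. One is a study in Bhutan, where "only 25% of health workers had adequate knowledge of snakebite management"; the same study gives 63% for medical doctors. The 13% is awareness of the four main venomous snakes in a mixed sample of farmers, teachers, medical residents and students. All three are shares of people in other settings, not item scores, so using them as p is an assumption.

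**2. An unclear item that is often guessed correctly.** Take a two-choice item that a share c of participants do not understand. They guess and are right half the time; the others are right 90% of the time (all assumed). Percentage correct is 0.5c + 0.9(1 − c).

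- c = 0.5: 0.25 + 0.45 = 0.70. Flagged with probability 0.048 (n = 20) to 0.000 (n = 100).
- c = 0.6: 0.30 + 0.36 = 0.66. Flagged with probability 0.103 to 0.001.
- c = 0.7: 0.35 + 0.27 = 0.62. Flagged with probability 0.190 to 0.010.

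Each of these items is unclear to half or more of the participants, and most would pass.

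**3. Possible effect on the measured gain.** Assume a 20-item test. Twelve items go from 70% to 90% correct. Eight hard items go from 25% to 85%. The gain is 12 × 0.20 + 8 × 0.60 = 2.4 + 4.8 = 7.2 items. Now let g be the gain per hard item after rewording, so that the total is 2.4 + 8g.

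- Difficulty unchanged, g = 0.60: 7.2 items, no loss.
- Intermediate, g = 0.45: 2.4 + 3.6 = 6.0 items, a loss of 1.2/7.2 = 17%.
- Made easier, 60% to 90%, g = 0.30: 2.4 + 2.4 = 4.8 items, a loss of 2.4/7.2 = 33%.

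The loss depends wholly on what rewording does to difficulty. Checks 1 and 2 do not depend on that.

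**The case against.** The strongest reply is that the operative sentence speaks of questions unclear to half the participants, not of questions that half get wrong, so percentage correct may only be a first screen. The text does not equate the two outright, and this caution stands. But no other measure is given for the rule, so the equation remains the natural reading.

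A reader might go further and infer that the rule biases the training effect towards zero. The article does not support that. It says items are reworded or rewritten, not simplified or dropped. Whether an item is kept is decided separately, by expert relevance ratings. Rewriting an item that really is unclear could even make it more sensitive to training. The direction and size of any bias are therefore open.

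A reader might also infer that the key guideline items will be flagged for all providers. The 63% cited for doctors speaks against that for the Medical Officer form: at that level a clear item is flagged with probability 0.165 or less.

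Clarity is also checked elsewhere. The advisory committee comments on ease of understanding, there is a pilot and a pre-test, and a readability score is planned: "To confirm the understanding of the questions, the Simple Measure of Gobbledygook (SMOG) score will be used". These help, but a readability score is computed from the text and the committee gives expert opinion. Nothing says that any of these checks overrides the 50% rule.

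Finally, training is to cover snakebite management as a whole, with Phase III gaps as an addition, so its content does not hang on these items alone. That stands and limits the consequence.

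**Conclusion.** The concern holds in a limited form. The stated rule uses a measure that cannot separate lack of knowledge from unclear wording, and it covers the provider knowledge questionnaire. On the natural reading it will almost always flag a clear item that about a quarter of respondents can answer, and it can pass items that most do not understand. This is likelier to matter for peripheral workers than for Medical Officers.

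The harm to Phase III and to the summative index is conditional: it arises if rewording makes flagged items easier or cues the answer. Its size is unknown and runs from none to one third of the gain under the assumed 20-item illustration. The flagging probabilities rest on an assumed pilot size and on treating cited shares of people as item scores.

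The primary outcomes (incidence and case fatality) and the listed secondary outcomes do not use these items and are not affected.

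**What to change.** Replace the difficulty-index rule with two separate statements:

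- **Clarity.** In the pilot and pre-test, flag an item for rewording when 50% or more of participants report, or show on probing, that they did not understand what was being asked.
- **Difficulty.** Report percentage correct for each item as a description only. Do not reword an item that was understood and is based on the treatment guideline solely because most participants answered it wrongly.

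The change has to be made before the tools are finalised. It costs a sentence or two in the protocol and a short comprehension check, such as a tick-box or a brief probe per item, in a pilot and pre-test that are already planned. The downside is slightly longer pilot sessions.
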